## Abstract

**Background:**

Many patients with chronic heart failure (CHF) are critically ill and experience increased thirst. Study aims are to develop and evaluate a nurse-based counselling intervention to promote self-care competencies related to thirst in hospitalised patients with advanced CHF eligible or listed for heart transplantation.

**Methods:**

A mixed-methods approach will be adapted with three study phases: (1) development of the nurse-based counselling intervention, (2) feasibility testing and training of nurses, and (3) implementation of the intervention and, evaluation of initial effects and process measures. In phase (1), interviews with hospitalised patients with advanced CHF listed for heart transplantation (*n* = 10), focus groups (*n* = 2) and a Germany-wide survey with nurses will be performed. In phase (2), experts experienced with caring for patients with advanced CHF and patients with advanced CHF will be consulted for content validation and pretest of the counselling intervention. The training concept for nurses will be evaluated using questionnaires. In phase (3), a pilot before–after study will be conducted (*n* = 60). Primary patient-related outcome for the pilot study is thirst intensity using a numeric rating scale. Furthermore, a process evaluation (interviews with patients [*n* = 10], survey with nurses and physicians) will be performed. Quantitative data will be analysed descriptively, and qualitative data will be analysed using content analysis. Mean values of thirst intensity of the individual measurement points will be evaluated as interrupted time-series analysis using regression analyses.

**Conclusion:**

The development and implementation of a counselling intervention is influenced by various factors. Therefore, it is important to consider all factors throughout the process from development to evaluation.

**Supplementary Information:**

The online version of this article (10.1007/s00063-023-01091-y) includes the SPIRIT 2013 Checklist.

## Background

Patients with advanced chronic heart failure (CHF) are critically ill and often experience increased thirst due to their disease and therapeutic regiment [1]. Severe thirst can lead to distress and influence patients’ quality of life [15, 26]. More than 70% of patients with CHF may experience moderate to severe thirst distress [8, 26, 28]. Factors associated with thirst intensity are for example the severity of heart failure, fluid restriction and high doses of diuretics [25]. Adherence to fluid restriction is particularly relevant for those with advanced CHF and severe symptom burden [13].

A heart transplantation is one of the last therapeutic interventions for patients with advanced CHF. The waiting period is often associated with a long hospital stay, high emotional burden and strict adherence to dietary and treatment-related behaviours [5, 20, 21]. An increased feeling of thirst can influence the adherence to therapy-related interventions [24] and additionally increase patients’ stress during this time. Patients with CHF often lack options for alternative interventions to reduce thirst other than drinking fluids. In a study by van der Wal et al. [25] with 216 participants, 56% reported to drink more when they are thirsty, while 12% had no strategies to reduce thirst. Nine participants (4%) indicated sucking ice cubes as an intervention strategy and three participants preferred chewing gum [25]. A survey with health professionals (*n* = 42) in Australia found that the most recommended intervention was ice cubes (95%) [2].

Currently, there is little evidence about intervention strategies to reduce thirst in patients with CHF. A pilot study (*n* = 71) testing gum chewing as an intervention showed a significant reduction in thirst after 4 and 14 days [3]. Hudiyawati and Suswardany [10] analysed the effect of frozen strawberries compared with ice cubes (*n* = 34). Thirst intensity (visual analog scale [VAS], 0–10) decreased in both groups (*p* = 0.001). However, these studies present only limited evidence for a small number of interventions to alleviate thirst and do not address the individual needs and preferences of patients. Chewing gum as an example is not suitable for patients with swallowing disorders, while ice cubes can be painful for patients with sensitive teeth. Chen et al. [7] published a scoping review in which further single interventions, e.g. lemon water spray, ginseng plum decoction or black plum soup were mentioned. Studies were conducted in China and are not accessible.

Evidence-based counselling by nurses to promote self-care skills related to thirst in hospitalised critically ill patients with advanced CHF eligible or listed for a heart transplantation may support patients in obtaining information and selecting appropriate interventions to relief thirst. Self-care is a decision-making process that is influenced by actions, aiming to maintain physiological stability and facilitate symptom awareness and management [16]. It is also known that the onset of symptoms can negatively influence self-care behaviour [17]. For example, being stressed of feeling thirsty can have an impact on adherence to prescribed fluid restriction [24].

The development and evaluation of a nurse-based counselling intervention has not yet been investigated, neither nationally nor internationally.

## Aims and research questions

Aims of the study are (1) to develop a nurse-based counselling intervention to promote self-care competencies related to thirst in hospitalised patients with advanced CHF eligible or listed for heart transplantation, (2) to test the feasibility and (3) the initial effects of the intervention.

Research questions areHow do hospitalised patients with advanced CHF experience their thirst? What are patients’ needs and requirements for information and what is their experience of health professionals providing information and advice on thirst as a symptom in the context of their disease? Which issues do they consider important in relation to thirst?Which information about thirst is provided by nurses on transplantation wards to patients with advanced CHF? Which issues do nurses consider important in relation to thirst?What is the feasibility of a counselling intervention to promote self-care competencies on thirst in hospitalised patients with advanced CHF failure eligible or listed for a heart transplantation?What are the initial effects of the counselling intervention and which factors influence its implementation?

## Methods

Data are reported following the recommendations for reporting study protocols of clinical intervention studies (SPIRIT) [6].

This study is based on the recommendations of the Medical Research Council (MRC) for the development and evaluation of complex interventions [19]. As recommended the research questions will be answered using a mixed methods approach. The project is divided into three study phases: (1) development of a nurse-based counselling intervention, (2) testing of feasibility and training of nurses and (3) implementation and evaluation of initial effects (Fig. 1).

**Fig. 1 Fig1:**
[figure not shown]
Study phases and methods

The study phases are not to be understood as strictly sequential phases as they can partly run in parallel. Figure 2 shows the overall study outline over time. In phase 1 (development of the counselling intervention), a systematic literature review (not reported here), 10 interviews with hospitalised patients with advanced CHF listed for heart transplantation, two focus groups with nurses and a Germany-wide survey with nurses will be performed. In phase 2 (feasibility of the counselling intervention), six to eight experts experienced in the care of patients with chronic heart failure (e.g. working group for Nursing Research in Cardiology/Cardiac Surgery, federal working group of nursing experts in heart failure in Germany) will be consulted for content validation. Subsequently, two guided interviews will be conducted with patients, who had a heart transplantation and experienced thirst during their disease. Goals of the interviews are to assess the comprehensibility, completeness and applicability of the counselling intervention. In addition, feasibility of the counselling intervention will be tested by two trained nurses on the wards of the included hospitals with four patients with advanced CHF waiting for a heart transplantation. To assess the feasibility and applicability of the intervention, a qualitative survey of the nurses and patients will be performed after the pretest of the counselling intervention. A training concept for nurses will be carried out and evaluated by means of a questionnaire.

**Fig. 2 Fig2:**
[figure not shown]
Study process including all study phases and measurement time points (t0-t2)

This protocol focusses on the third phase, where the intervention will be implemented in practice and the initial effects of the new counselling intervention will be tested in a pilot before–after study. In addition, a process evaluation will be conducted. Data collection will be performed in two university hospitals.

## Pilot before–after study

The study will be designed as a pilot before–after study (interrupted time series analysis). Measurements will be conducted at three time points each before (before study [bs]) the training of the nursing staff (t0bs, t1bs, t2bs) and after (after study [as]) the implementation of the counselling intervention (t0as, t1as, t2as; Fig. 2).

### Sample and recruitment

Hospitalised patients with advanced CHF who are eligible or listed for heart transplantation will be included. Based on the study by Allida et al. [3], the case number estimate was calculated using a thirst intensity (NRS) of 4.2 ± 2 (baseline data). In order to detect a mean difference of one point with a standard deviation of 2 in thirst intensity (two-sided tests, significance level = 0.05 and power = 0.80), a sample of 67 patients per group is needed in a future randomised controlled trial. In order to determine feasibility and gather information for the future main effectiveness trial, we will first conduct a pilot study with a total of 60 patients (30 per group; two-sided tests, significance level = 0.30 [sic!] and power = 0.80).

Patients will be recruited consecutively. All patients treated at the heart failure units of the two participating university hospitals during the period of data collection who meet all inclusion criteria will be included in this study. Measurement will be conducted at two time points: before implementation of the counselling intervention (group I) and after implementation (group II).

### Inclusion and exclusion criteria

Patients with the following criteria will be included: advanced CHF, age ≥ 18 years, eligible or listed for heart transplantation, hospital stay (expected > 14 days), understanding and speaking the German language and available written informed consent.

Patients will be excluded if they are disorientated, mechanically ventilated, have an implemented (left) ventricular assist device (L)-VAD or are in the palliative phase. For the “after group”, patients who were already recruited for the “before group” will also be excluded.

### Outcome parameters

Primary outcome is thirst intensity, which is measured using a numerical rating scale (NRS; 0 = no thirst, 10 = strongest thirst).

Secondary outcomes areThirst distress using the Thirst Distress Scale for patients with heart failure (TDS-HF) [29],Thirst frequency: At what time of day was the feeling of thirst strongest? (morning, afternoon, evening, night),Dry mouth with the short form of the xerostomia inventory (XI) [23],Fluid restriction (yes/no, amount),Health-related quality of life using the short form version of the Kansas City Cardiomyopathy Questionnaire (KCCQ-12) [22],Depressivity and anxiety using the ultrashort form of the German version of the Patient Health Questionnaire (PHQ-D) [12],Satisfaction with information transfer (NRS, 0 = not satisfied to 10 = very satisfied),Degree of informedness (NRS, 0 = not informed to 10 = very informed) andAdapted Patient Involvement in Care Scale (PICS) [18]

In addition, process-related data such as questions about thirst counselling, interventions implemented to alleviate thirst as well as sociodemographic and disease-related data will be assessed. Table 1 shows all outcome parameters according to the measurement time points.

**Table 1 Tab1:** Measurement parameters: before–after study

	t0	t1	t2
Age	x	–	–
Gender	x	–	–
Education	x	–	–
Social support	x	–	–
Weight	x	x	x
Current medications	x	x	x
LVEF	x	–	–
Fluid restriction and amount	x	x	x
Co-morbidities	x	–	–
NYHA classification	x	x	x
Weather (temperature)	x	x	x
Documentation analysis for recording thirst and used interventions	x	x	x
Thirst intensity (NRS)	x	x	x
Thirst distress (TDS-HF)	x	x	x
Thirst frequency	x	x	x
Dry mouth (XI)	x	x	x
Health-related quality of life (KCCQ)	x	–	x
Depressivity and anxiety (4-item PHQ-D)	x	–	x
Conducted interventions	x	x	x
Informedness	x	x	x
Thirst counselling	–	–	x
Satisfaction with information transfer	–	–	x
Adapted Patient Involvement in Care Scale (PICS)	–	–	x

*KCCQ* Kansas City Cardiomyopathy Questionnaire, *LVEF* Left ventricular ejection fraction, *NRS* Numeric rating scale, *NYHA* New York Heart Association, *PHQ‑D* Patient Health Questionnaire–Deutsch, *PICS* Patient Involvement in Care Scale, *TDS-HF* Thirst Distress Scale for patients with heart failure, *XI* Xerostomia inventory

### Data collection

Baseline data will be collected before the training of nurses. Patients who meet all inclusion criteria within the first 3 days after admission to the ward and who are expected to stay at least 14 days (based on nurses’ judgement) will be included in the study.

If the patients have provided informed consent, all disease-related data from the hospitals’ patient documentation system (Table 1) will be collected and a questionnaire will be handed out to the patients, which is completed independently by the patient. Seven and 14 days after inclusion, participants will receive further questionnaire and the above-mentioned data are retrieves from the patient’s file.

If the planned sample size is reached, training of nursing staff on the counselling intervention will be performed and all participants will receive individual counselling by the nursing staff. Follow-up data will be collected after a 7-day individual intervention period of each participant.

#### Nurse-based counselling intervention (Table 2)

At least 50% of the nurses of the included wards at the two university hospitals who have a minimum workload of 19.25 h per week (50%) will be trained for the counselling intervention. Counselling will include the following content: basic information about thirst as a symptom of CHF and CHF therapy, assessment of thirst (occurrence, quality, intensity, distress), interventions already used by patients, suggestions for preventive interventions, shared decision making on interventions for individual participants. Patients will also receive information materials after counselling and nurses will record counselling in the patient chart.

**Table 2 Tab2:** Intervention description based on the Template for Intervention Description and Replication (TIDieR) Checklist [9]

*BRIEF NAME*	Nurse-based counselling to promote self-care competencies concerning thirst in patients with advanced chronic heart failure eligible or listed for heart transplantation
*WHY*	The intervention aims to enable patients with advanced chronic heart failure eligible or listed for heart transplantation to choose and perform individual interventions to reduce thirst. The intervention is based on the systematic literature review, interviews with patients as well as the focus group and survey with nurses. The situation-specific theory of Heart Failure Self-Care is used as theoretical framework [16, 17]. Counselling follows a solution-focused approach [4, 27]
*WHAT*	*Contents of counselling:* assessment of thirst (occurrence, quality, intensity, distress); interventions already used by participants; thirst and heart failure; preventive interventions; shared decision making; use of information materials; documentation of the counselling
*WHO PROVIDES*	Trained staff nurses
*HOW*	Individual face-to-face counselling
*WHERE*	On the ward
*WHEN and HOW MUCH*	One counselling session within 7 days after inclusion
*TAILORING*	Personalized counselling, due to different individual perception of thirst and various possible interventions
*HOW WELL*	Patient evaluation after 7 and 14 days

### Economic outcomes

For cost analysis of the research project, cost components will be collected prospectively. Costs for materials and training, duration of intervention, time resources of the nursing staff, number of employees involved in the project and additional interventions that result from the counselling concept will be captured.

## Process evaluation

For the process evaluation, interviews will be conducted with patients who received counselling, a survey with nurses who performed counselling and with physicians involved in the provision of care on the wards. In addition, contextual factors will be assessed. Fidelity of the intervention will be assessed using a short protocol.

### Interviews with patients who received counselling

Five randomly selected patients per included hospital (*n* = 2) who received counselling by nurses will be asked to take part in an interview. The individual interviews will be conducted after t1as. The interviews will focus on patients’ experiences with the provision of information and counselling, the applicability of the recommended interventions to alleviate thirst, as well as possible influencing factors (promoting and inhibiting factors) of the implementation.

### Survey with nurses

Six months after the start of the implementation of the counselling concept, nurses who received the training will be invited to fill out a questionnaire, addressing the number of counselling sessions and their duration, the learning effect of the training, practicability of contents, framework conditions, influencing factors, facilitating factors and barriers as well as applicability of the concept.

### Survey with physicians

Also, 6 months after the start of the implementation of the counselling concept, treating physicians will receive an adapted questionnaire assessing knowledge, attitude, assessment of effects of the counselling concept.

### Context factors

To describe context factors on the wards included in the study, the following data will be collected:Nurses’ experience levels and qualifications,Number and characteristics of patients on the ward andDescription of the environment in which counselling takes place

In addition, after the nurse training, protocols will be created in order to compare planning and actual implementation of the training.

### Data analysis

Quantitative data will be analysed using Statistical Package for Social Science (SPSS) Statistics (IBM Corp. Released 2022, IBM SPSS Statistics for Windows, Version 29.0.0.0, Armonk, NY, USA). The analysis will initially be performed descriptively and results will be presented as absolute and relative frequencies. Ordinal and metric data will be checked for normal distribution and shown as median (IQR) or mean (standard deviation).

The analysis of the measurement instruments TDS-HF, XI, KCCQ, PHQ‑D and PICS will be conducted both at item level and at scale level. In order to be able to detect differences due to the implementation of the counselling concept, depending on the data level, either a t-test, Mann–Whitney U test, chi-square (Χ^2^) test according to Pearson or exact test according to Fisher will be performed. Mean values of thirst intensity (NRS) of the individual measurement points will be evaluated as interrupted times series analysis using regression analyses.

Transcribed qualitative data (interviews with patients) will be analysed using content analyses [11] applying MAXQDA Standard 2022 (VERBI GmbH, Berlin, Germany). As recommended in the MRC Framework, quantitative and qualitative data will be combined related to the process relevant outcomes variables to evaluate factors that may have an influence on the implementation of the intervention [14].

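### Group differences between two consecutive, non-randomised cohorts are tested without baseline or site adjustment and credited to the counselling, although the t0 values needed for adjustment are collected

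*Protocol article*

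**What the plan says.** **Design.** Under Sample and recruitment, the comparison is "before implementation of the counselling intervention (group I) and after implementation (group II"), and "Patients will be recruited consecutively". Inclusion and exclusion criteria adds, for the after group, that "patients who were already recruited for the “before group” will also be excluded". Data collection separates the phases in time: "If the planned sample size is reached, training of nursing staff on the counselling intervention will be performed". The cohorts are therefore independent, sequential and not randomised. Two university hospitals take part.

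**Analysis.** Data analysis introduces the tests with "In order to be able to detect differences due to the implementation of the counselling concept, depending on the data level, either a t-test". The full list is "either a t-test, Mann–Whitney U test, chi-square (Χ^2^) test according to Pearson or exact test according to Fisher will be performed". The next sentence gives thirst intensity a further analysis: an interrupted time series, by regression on the means of the individual measurement points. The article names no covariate for either analysis.

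**Data available.** In Table 1, thirst intensity, TDS-HF, thirst frequency, XI, informedness, NYHA class, fluid restriction, medications and "Weather (temperature") are recorded at t0, t1 and t2. KCCQ and the 4-item PHQ-D are recorded at t0 and t2. Satisfaction with information transfer and PICS are recorded at t2 only.

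**Known drivers of thirst.** The Background states: "Factors associated with thirst intensity are for example the severity of heart failure, fluid restriction and high doses of diuretics".

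**The concern.** In a before-after comparison of different patients, a two-sample test asks only whether the cohorts differ. It cannot tell whether the difference comes from counselling, from sicker or less restricted patients in one phase, or from the period. The analysis text nevertheless reads the difference as due to implementation.

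The variables that could partly account for such a shift are already collected, and the article itself links two of them (severity and fluid restriction) to thirst. The t0 value of each outcome is the most useful of all. It is taken at inclusion, while the counselling session falls within the following 7 days. A gap already visible at t0 cannot be an effect of counselling, yet a test on t1 or t2 values alone would count it as one.

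The error can run either way: a shift can imitate an effect or hide one. The Conclusion offers the results as a basis for a later randomised trial, so a confounded estimate would carry into that decision.

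**Working it through.** **Inputs.** From Sample and recruitment: difference 1 point, SD 2, 30 per group, two-sided alpha 0.30 for the pilot; 67 per group at alpha 0.05 for the future trial; power 0.80. Assumed, because the article does not give them: a cohort shift of 0.25, 0.5 or 1.0 NRS points at follow-up, and a correlation rho between t0 and follow-up of 0.5 (range 0.3 to 0.7).

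**1. The plan's own sample sizes.**
- Normal approximation, n = 2·SD²·(z₁₋α/₂ + z₀.₈)²/δ²: at alpha 0.05, 2·4·2.802² = 62.8, so 63; at alpha 0.30, 2·4·1.878² = 28.2, so 29.
- t-test: 63.8 and 28.3, so 64 and 29.
- t-test size divided by the Mann–Whitney relative efficiency 3/π: 66.8 and 29.6, so 67 and 30.

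The last variant matches both stated figures. They therefore fit an unadjusted two-group comparison of thirst intensity.

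**2. Rejection when counselling has no effect but the cohorts differ.** SE = 2·√(2/30) = 0.516, with 58 degrees of freedom. The critical values are 1.046 (alpha 0.30) and 2.002 (alpha 0.05). The noncentrality is shift/SE.

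| Shift at follow-up | Noncentrality | Rejects, alpha 0.30 | Rejects, alpha 0.05 |
|---|---|---|---|
| 0 | 0 | 30% | 5% |
| 0.25 | 0.48 | 35% | 8% |
| 0.5 | 0.97 | 49% | 16% |
| 1.0 | 1.94 | 82% | 48% |

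A 1-point shift equals the whole target difference, so its row is simply the power of the test.

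**3. What adjusting for t0 does to the bias.** If the cohorts differ by b₀ at t0 and b₂ at follow-up, ANCOVA leaves a bias of b₂ − rho·b₀ (the within-group slope is rho because both SDs are 2). Simulated rejection rates, with rho 0.5, no true effect and 5,000 runs per setting:

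| b₀, b₂ | Remaining bias | Alpha 0.30: unadjusted / ANCOVA | Alpha 0.05: unadjusted / ANCOVA |
|---|---|---|---|
| 1, 0.5 | 0 | 48% / 30% | 15% / 5% |
| 0.5, 0.5 | 0.25 | 49% / 37% | 16% / 9% |
| 1, 1 | 0.5 | 81% / 54% | 48% / 18% |

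Adjustment restores the nominal level when the shift fades in line with rho. When the shift persists in full, adjustment halves the bias.

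**4. What it does to precision.** The residual SD is 2·√(1 − rho²) = 1.91, 1.73 and 1.43 for rho 0.3, 0.5 and 0.7. With 30 per group and a 1-point effect (noncentral t):
- alpha 0.30: power 0.84, 0.88 and 0.95, against 0.815 unadjusted;
- alpha 0.05: power 0.51, 0.59 and 0.76, against 0.48 unadjusted.

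These gains are for the t0 value alone. Further covariates have not been quantified.

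**The case against.** The strongest counter-argument is that the primary outcome has its own model. The time-series regression uses the means at t0, t1 and t2 in each cohort, so baseline level is not ignored there. This stands: a reader might infer that thirst intensity is judged only by a t-test at follow-up, and the article does not say so. But that regression works on means, names no patient-level covariate, and has three visits over 14 days per cohort. It cannot show whether thirst was drifting over calendar time. The secondary outcomes have no such model, so the point is strongest for them, although the figures above are for NRS thirst, the only outcome with a stated SD and target difference.

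Second, this is a pilot seeking initial effects, and a condensed article may leave covariate lists to the full protocol. That lowers the stakes. It does not dispose of the point, because the article itself fixes the tests and the causal reading.

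Third, some stronger statements are tempting but unsupported:
- Two identical populations would differ at t0 by at least 0.5 points in 33% of trials (SE 0.516). A reader might take this as the size of the bias. It is chance imbalance, which a randomised trial of this size would share and which the test's alpha already covers.
- A reader might infer that baseline adjustment cures the problem. Step 3 shows that a persistent shift is only reduced.
- Temperature looks an obvious covariate, but with sequential phases it may be collinear with period and cost precision.
- A fixed recruitment split per hospital sits badly with the consecutive inclusion of all eligible patients.

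**Conclusion.** The point holds in this form: the named group comparisons take no account of baseline or site in a sequential, non-randomised design, their differences are attributed to implementation, and the data for a better comparison are already being collected. The regression on thirst means does not close the gap.

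For NRS thirst, a shift of 0.25 to 1.0 points with no counselling effect gives rejection rates of 35% to 82% at alpha 0.30 and 8% to 48% at alpha 0.05. The shifts are assumptions. Nothing in the article shows that one will occur, or its direction, so this measures vulnerability, not expected bias. The power gain also rests on an assumed correlation. The change is a worthwhile, cheap improvement; its absence does not invalidate the pilot.

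**What to change.** - For every outcome measured at t0, make the group comparison an individual-level ANCOVA (ordinal or logistic regression for categorical outcomes) with group, the outcome's own t0 value and hospital.
- For NRS thirst, add t0 NYHA class and t0 fluid restriction. Use only the t0 value of fluid restriction, because it is also a secondary outcome and may change afterwards. Add temperature in a sensitivity analysis only.
- Report adjusted estimates with confidence intervals and keep the unadjusted tests as descriptive.
- State that adjustment reduces but does not remove confounding by period, and that satisfaction and PICS, measured only at t2, have no baseline of their own.

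**Cost.** Analysis wording and a few degrees of freedom out of 60 patients, hence the short covariate list. No new data, patients or recruitment quota are needed. Hospital is not a row in Table 1 but is known from the site.

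### The interrupted time series regression named for thirst intensity does not fit a design with two separate patient cohorts, each followed for 14 days from inclusion

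*Protocol article*

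**What the plan says.** - **Outcome** (Outcome parameters): "Primary outcome is thirst intensity, which is measured using a numerical rating scale".
- **Analysis** (Data analysis): "Mean values of thirst intensity (NRS) of the individual measurement points will be evaluated as interrupted times series analysis using regression analyses". The Abstract repeats this, and the section Pilot before–after study puts the same label on the design.
- **Measurement points** (Pilot before–after study): "Measurements will be conducted at three time points each before (before study [bs]) the training of the nursing staff (t0bs, t1bs, t2bs) and after" the counselling has been implemented, again three points (t0as, t1as, t2as).
- **Timing** (Data collection): the first questionnaire is handed out once consent is given. Then: "Seven and 14 days after inclusion, participants will receive further questionnaire".
- **Who is measured**: recruitment is consecutive, with group I before and group II after implementation (Sample and recruitment). For the after group, "patients who were already recruited for the “before group” will also be excluded" (Inclusion and exclusion criteria).
- **When counselling happens** (Table 2): "One counselling session within 7 days after inclusion".
- **Sample size** (Sample and recruitment): 30 per group to detect 1 point with SD 2, two-sided alpha 0.30, power 0.80, as a comparison of two groups.

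Data analysis also lists t, Mann–Whitney, chi-square and Fisher tests for differences due to the implementation, chosen by data level and without naming an outcome.

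**The concern.** An interrupted time series takes one outcome series in calendar time, estimates the trend before a known break, and projects it forward as the counterfactual. Nothing in this design supplies that trend. Each of the six means pools patients included on many calendar dates. The before-phase slope is therefore the course of thirst during a hospital stay, not a secular trend on the ward. Going from t2bs to t0as changes the patients and resets their clock to day 0, so it is not one more step along a series. The t0as point would fall in the after segment although the patient has generally not yet been counselled.

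The pilot is meant to inform a later randomised trial. An effect estimate that is shrunken or has the wrong sign would misinform that trial.

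**Working it through.** **Inputs from the protocol article.** Baseline mean 4.2, SD 2, difference 1 point, 30 per group, two-sided alpha 0.30 (pilot) and 0.05 (future trial), visits at days 0, 7 and 14, different patients before and after.

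**Assumptions not in the article.** In-stay trend b in NRS points per week, the same in both cohorts; within-patient correlation 0.3 to 0.7; the six means placed at times 1 to 6; a segmented regression with intercept, trend, level change and slope change. Six means less four parameters leaves 2 residual degrees of freedom (two-sided 5% critical t = 4.30).

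**Step 1, the stated sample size.** n per group = 2·SD²·(z for alpha + z for power)²/difference² = 8·(1.036 + 0.842)² = 28.2, so 29. The exact t calculation also gives 29 and the Mann–Whitney variant gives 30. The stated 30 is reproduced. For the future trial the three methods give 63, 64 and 67; the stated 67 matches the Mann–Whitney variant. The sizing therefore rests on two independent groups. With 30 per group the SE is 2·√(2/30) = 0.52, and power for 1 point at alpha 0.30 is about 82%.

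**Step 2, no effect and a common trend b.** The before means 4.2, 4.2+b, 4.2+2b at times 1–3 project to 4.2+3b at time 4. The after means start again at 4.2. Level change = 4.2 − (4.2+3b) = −3b. Slope change = b − b = 0.

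**Step 3, true reduction of 1 point at t1as and t2as.**
- Flat course: after means 4.2, 3.2, 3.2. Slope = (3.2 − 4.2)/2 = −0.5; mean 3.533; fitted value at time 4 = 3.533 + 0.5 = 4.033. Level change = 4.033 − 4.2 = −0.17; slope change = −0.5. Without the slope-change term the level change is +0.08.
- b = −0.5: after means 4.2, 2.7, 2.2. Slope −1.0; mean 3.033; fitted value at time 4 = 4.033; projection 4.2 − 1.5 = 2.7. Level change = +1.33, the wrong sign; slope change = −1.0 − (−0.5) = −0.5.

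**Step 4, rejection rates for the level change.** Simulation, 20,000 trials per scenario; ranges are over correlation 0.3–0.7.

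| Scenario | Level change | p<0.05 | p<0.30 |
|---|---|---|---|
| No effect, b = 0 | 0 | 6–11% | 34–47% |
| No effect, b = −0.25 | +0.75 | 14–26% | 57–71% |
| No effect, b = −0.5 | +1.5 | 35–58% | 88–96% |
| 1-point reduction, b = 0 | −0.17 | 2–3% | about 23% |

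The flat row is the reference: even without bias the level test exceeds its nominal size, because regression on means ignores that the same patients supply three points.

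**Step 5, the slope change.** With no effect it holds its size (about 5% and 30%). With the 1-point reduction it rejects in about 48–57% at alpha 0.30, against about 82% for the two-group comparison in step 1.

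**The case against.** **The coding is not given.** The article states no time axis, parameter count or error structure, and an article may leave these to a fuller document. If the means were regressed on group and day, any common in-stay trend would cancel and the group contrast would be usable. This stands as a limit: the step 2–4 results hold only for a sequential axis. That axis is what the label implies, however, and a group-by-day regression would not be an interrupted time series, so the wording needs correcting either way.

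**Not every term is wrong.** A reader might infer that whatever this regression returns for the intervention is an artefact. That does not hold. The slope change equals the group-by-day interaction, keeps its size and has the correct sign. Its weakness is low power.

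**It may not be the only test of the NRS.** A reader might infer that the primary outcome has no other planned analysis. The generic two-group tests in Data analysis exclude no outcome and could cover thirst intensity, which would agree with the sizing. What remains is that the time series regression is the only method tied to thirst intensity by name, and no rule says which result prevails.

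**Timing of t0as is inferred.** It follows from the first questionnaire being given at consent and counselling taking place during the next 7 days. The article does not say so outright, and the figure showing the timing is not available.

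**Pilot status.** The study seeks initial effects, and 0.30 is a sizing value, not a declared analysis threshold. This lowers the stakes but does not make the named method fit.

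**Conclusion.** The point holds as a mismatch between a stated method and the design. The article names an interrupted time series regression on means for its primary outcome, while the design provides two consecutive cohorts of different patients followed from inclusion.

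On a sequential axis, the level change measures the in-stay course of thirst with its sign reversed and multiplied by three, and it largely misses the effect on which the pilot is sized. The size of the error depends on an in-stay trend that the article does not give. If the course is exactly flat and there is no effect, the level estimate is unbiased. A real 1-point effect is still returned as −0.17, on the reading that t0as precedes counselling. The sample-size figures are not at fault.

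**What to change.** 1. Remove the interrupted time series label from the Abstract, Pilot before–after study and Data analysis, and describe the design as a before–after comparison of two consecutive cohorts.
2. Replace the regression on means with one named primary analysis at patient level: the after-minus-before difference in post-counselling NRS, adjusted for each patient's own t0 NRS. ANCOVA at t2 would serve; so would a repeated-measures model with group, visit (t1, t2), group by visit and correlated errors within patient. Report the estimate with a confidence interval. At an assumed correlation of 0.6, baseline-adjusted ANCOVA rejects in about 91% at alpha 0.30, against 81% for the unadjusted test at t2.
3. State that t0as is collected before the patient's counselling, since the adjustment depends on it, and say what role the generic two-group tests have for thirst intensity.
4. State that secular change between the two cohorts is not controlled.

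The cost is rewording of the design and analysis paragraphs. The data and visits are unchanged, and SPSS, already named, fits either model.
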